### Aim

Thus, the primary aim is to investigate the impact of 3 levels of personalized dietary feedback and support on changes in diet quality, as measured by the Australian Recommended Food Score (ARFS). The secondary aim is to investigate intervention reach, participant engagement, retention, satisfaction, and cost-effectiveness.

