### Randomization

Eligible participants will be randomly allocated (1:1:1) to a control group or 1 of 2 intervention groups. Randomization will occur in permuted blocks using random blocks of varying size and be stratified by postcode location (using the Monash Modified Model) [25], sex, and BMI (18.5-24.9 kg/m^2^ vs ≥25 kg/m^2^). Randomization will be coded by an independent statistician who will provide the coding to the software developers to program the web-based environment. The research team will remain blinded to the randomization code.

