### Sample Size

The sample size calculation was based on detecting changes in the primary outcome of diet quality score (AFRS), with adequate power to assess differences in daily servings of fruit and vegetables. The study aims for a between-group increase in ARFS of 2.2 (baseline SD 9.6) and fruit and vegetables serves per day of 0.56 (baseline SD 2.4) compared with no change in the control group [53]. To detect this between-group AFRS difference with an alpha of .05 and 80% power, 300 participants per arm across 3 arms are required, totaling 900 participants. Given that we also wish to examine this effect a priori in male and female subgroups separately, we will require 900 participants of each gender or 1800 in total. To allow for 10% loss to follow-up at 3 months, 20% at 6 months, and 30% at 12 months, the study requires a total sample of 2570 (1285 males and females each).

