### Statistical Analysis

The outcome effects will first be evaluated using independent *t* tests, followed by repeated measures within-group changes in the ARFS diet quality score and modeling between-group changes over time using the generalized linear mixed model. The model will be fitted with ARFS at all follow-up points as the outcome variable, with fixed effects for group, time, baseline ARFS, and time by group interaction. Covariates, including PA, sleep, smoking, and social desirability, will be included in the statistical model as potential confounders. Statistical significance of the primary efficacy analysis will be based on Hochberg multiple testing procedures with a family-wise error rate for each time point held at 2.5%. The main analysis will use a generalized linear mixed model with the outcome at all time points and intention-to-treat principle. Sensitivity analyses will be conducted with the last observation carried forward, with multiple imputations, and for completers only. Analyses will be performed using SAS version 9.4 or later (SAS Institute Inc). All variables will be checked for plausibility and missing values. Data will be presented as mean (SD) for continuous and count variables.

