### Health Economic Analysis

The economic analysis will be conducted from a health service perspective. Cost estimation will follow a categorize:quantify:value approach. In the absence of health service implications, the costs will reflect the resources required to generate, implement, and deliver the respective interventions. The valuation will be founded on the concept of opportunity cost, that is, the value of the benefit forgone in not employing labor, services, or materials in alternative uses. Market prices will be used as a proxy for this value. Labor costs will reflect relevant skills, such as dietician time and administration time, and will incorporate additional employee benefits such as superannuation. Services include expenditure such as Facebook advertising. Materials capture nonlabor cost items such as flyers. Costs will be reported separately and jointly.

If a statistically significant difference in AQoL-6D is found, a within-trial cost analysis will be conducted using quality-adjusted life years (QALYs) as the primary outcome. The incremental cost-effectiveness ratio (ICER) will report an incremental cost per QALY, reflecting the incremental outcome and cost differences between the comparator groups. The ICERs will be calculated as the arithmetic mean difference in cost between the intervention and control arm divided by the arithmetic mean difference in effect. Groups 2 and 3 will be compared individually with Group 1 and each other. If a significant change in AQoL-6D is not observed, the ARFS outcome measure will be used. If neither measure realizes a statistically significant change, the economic method will default to a cost-consequence analysis, with incremental costs reported against all primary and secondary outcomes. The economic analysis will be conducted, and the results will be reported in accordance with best practice guidelines [54,55].

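### If all three pairwise contrasts are in the Hochberg family, a Simes-based closed test at the same 2.5% ceiling rejects everything Hochberg rejects and more; the plan should name the family and choose accordingly

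*Protocol article*

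**What the plan says.** The Statistical Analysis section of the protocol article fixes the procedure and the level: significance "will be based on Hochberg multiple testing procedures with a family-wise error rate for each time point held at 2.5" percent. It does not list the hypotheses that share that 2.5%, and it does not say whether the level is one- or two-sided.

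Other sections point in two directions.

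- Towards three contrasts: the Aim is to "investigate the impact of 3 levels of personalized dietary feedback and support on changes in diet quality", and the Health Economic Analysis section states that "Groups 2 and 3 will be compared individually with Group 1 and each other".
- Towards two contrasts: the Sample Size section expresses the target effect as "compared with no change in the control group", and the Randomization section describes the design in the same terms: "Eligible participants will be randomly allocated (1:1:1) to a control group or 1 of 2 intervention groups".

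The design values are in the Sample Size section: "The study aims for a between-group increase in ARFS of 2.2 (baseline SD 9.6" points), and "with an alpha of .05 and 80% power, 300 participants per arm across 3 arms are required, totaling 900 participants". For separate analyses by sex, "we will require 900 participants of each gender or 1800 in total".

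**The concern.** With three arms and two-sided nulls of equal means, if two of the three pairwise nulls are true, the third must be true as well. The only intersection hypothesis is therefore the global null that all three means are equal. Once that has been rejected at 2.5%, each pair can be tested at the full 2.5% with strong family-wise control. Hochberg does not use this relation: unless all three p-values are at or below 2.5%, it asks for 1.25% on the second smallest or 0.83% on the smallest.

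What is at stake is power, not validity. If benefit rises with the level of support, the steps between neighbouring groups (2 v 1 and 3 v 2) are smaller than the step from Group 1 to Group 3. They show whether the fuller report with the website, and then the dietitian consultation, each add anything. They are also the contrasts that gain most in the stepped scenarios below.

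**Working it through.** **The plan's own figure.** Two-sided alpha 0.05, power 80%, difference 2.2, SD 9.6:

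n per arm = 2 × (1.960 + 0.842)² × 9.6² / 2.2² = 2 × 7.849 × 92.16 / 4.84 ≈ 299, against 300 stated. Allowing for 30% loss, 1800 / 0.70 gives 2572, against 2570 stated. The inputs are therefore read correctly. At 12 months they imply about 300 analysed per arm within each sex and 600 per arm with both sexes (1800 / 3).

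**Dominance with three two-sided contrasts.** Let a = 2.5% and p(1) ≤ p(2) ≤ p(3).

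- The Simes global step rejects if p(1) ≤ a/3 = 0.83%, or p(2) ≤ 2a/3 = 1.67%, or p(3) ≤ a = 2.5%. Each pair with p ≤ 2.5% is then rejected.
- Hochberg rejects all three if p(3) ≤ a. The Simes step also rejects, and all three are at or below a.
- Hochberg rejects the two smallest if p(2) ≤ a/2 = 1.25%. As 1.25% < 1.67%, the Simes step rejects, and both are at or below a.
- Hochberg rejects the smallest if p(1) ≤ a/3. This is also a Simes condition.

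Every Hochberg rejection is therefore kept. The reverse fails. With p = 0.010, 0.015, 0.40 Hochberg rejects nothing, while the closed test rejects two contrasts because 0.015 ≤ 0.0167. Both procedures rest on the same Simes inequality.

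**Size.** Normal-theory simulation, 500,000 trials per scenario, SD 9.6, two-sided, 2.5% family-wise. The true means for Groups 1/2/3 are assumptions; only the 2.2-point difference from control comes from the protocol.

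| Per arm | True means | Contrast | Hochberg | Closed Simes |
|---|---|---|---|---|
| 300 | 0/2.2/2.2 | each v Group 1 | 60.0% | 65.1% |
| 600 | 0/2.2/2.2 | each v Group 1 | 92.7% | 94.8% |
| 300 | 0/1.1/2.2 | adjacent | 13.7% | 18.5% |
| 300 | 0/1.1/2.2 | 3 v 1 | 57.6% | 59.0% |
| 600 | 0/1.1/2.2 | adjacent | 33% | 39.5% |
| 300 | 0/2.2/4.4 | adjacent | 69.7% | 71.4% |

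No Hochberg rejection was lost in any run. Family-wise error under the global null was 2.3% for both procedures at 300 per arm. Under the partial null 0/2.2/2.2 at 300 per arm it was 1.6% with Hochberg and 2.5% with the closed test.

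**Baseline adjustment.** The planned model includes baseline ARFS, which lowers the residual SD. The protocol gives no baseline to follow-up correlation r, so it is varied here: the SD is 9.6 × √(1 − r²), that is 9.6, 8.3 and 6.9 for r = 0, 0.5 and 0.7.

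- 300 per arm, 0/2.2/2.2: 60 to 65%, 76 to 80%, 92 to 94%.
- 600 per arm, 0/1.1/2.2, adjacent: 33 to 39.5%, 47 to 52%, 69 to 70%.
- 300 per arm, 0/1.1/2.2, adjacent: 14 to 18%, 20 to 26%, 32 to 39%.

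The gain shrinks where the contrast becomes well powered. It stays at 5 to 6 points where the contrast is still poorly powered.

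**Two contrasts with Group 1 only.** Neither null implies the other, and Hochberg on two p-values is the closed Simes test. There were no differences in any run.

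**The case against.** A reader might infer that the plan as written gives up power, and that switching to a closed test can only help. The document does not support that, for five reasons.

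- **The family is not stated.** The sample size is framed against control, which fits a two-contrast family in which nothing is given up. All three pairs are listed only for the cost-effectiveness ratios. A condensed article may leave the family to a fuller document, so the omission is not counted as a fault here. This stands, and it makes the point conditional.
- **The change can lose power if it enlarges the family.** If two contrasts with Group 1 were intended, applying the three-contrast closed test cuts power against control at 300 per arm and 0/2.2/2.2 from 68% (Hochberg on two) to 65%. At 0/1.1/2.2, Group 3 v Group 1 falls from 63% to 59%. This stands.
- **Not every closed test dominates.** With an omnibus F or chi-square first step, Hochberg rejects something the closed test misses in 0.6% (0/2.2/2.2) and 1.1% (0/1.1/2.2) of runs at 300 per arm. Dominance needs the Simes step.
- **Sidedness matters.** If 2.5% is one-sided, it is no longer true that any two nulls imply the third. The matching closed test still dominates, but unevenly: at 0/2.2/2.2 and 300 per arm, 2 v 1 rises from 69.8% to 74.9% and 3 v 1 only from 69.5% to 69.8%.
- **Hochberg is standard and valid here.** Its simulated family-wise error never exceeded 2.5%. Part of the gain comes from spending error that Hochberg leaves unused, so the realised rate does rise, though the ceiling does not.

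None of this defeats the conditional point: for three two-sided pairs, the Simes-based closed test is never worse than Hochberg at the same nominal level.

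**Conclusion.** The point holds in conditional form, as a minor efficiency improvement. If the family at each time point is the three two-sided pairwise contrasts, a reasonable reading of the aim, Hochberg is dominated by a Simes-based closed test at the same 2.5% ceiling. At the design effect the gain is about 5 percentage points per contrast at 300 per arm and about 2 at 600 per arm; for smaller adjacent differences it reaches about 6. These sizes rest on SD 9.6, equal arms, normal theory and the assumed means, and are mostly smaller after baseline adjustment. If the family is the two contrasts with Group 1, there is no gain and no reason to change.

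**What to change.** In the Statistical Analysis section, name the contrasts that share the 2.5% at each time point and state whether the level is one- or two-sided. Then:

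- If all three two-sided pairs are in the family, replace Hochberg at each time point with a Simes test of the global null at 2.5%, using the three pairwise p-values from the mixed model: reject if p(1) ≤ 0.83%, p(2) ≤ 1.67% or p(3) ≤ 2.5%. If it rejects, test each pair at 2.5%. Do not use an omnibus F test as the first step if the aim is to keep every Hochberg rejection.
- If only the two contrasts with Group 1 are in the family, keep Hochberg and do not add the third contrast for the sake of this change.
- If the tests are one-sided, the closed test must be built from the one-sided nulls; the rule above does not carry over.

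The cost is a sentence or two, settled before any unblinded analysis, and trivial programming. No extra participants are needed, and the nominal family-wise level is unchanged, although the realised rate moves closer to 2.5%.

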### Outcome Measures

Outcome measures will be completed via the Aim4Me website at baseline and at 3, 6, and 12 months, along with a process evaluation (Multimedia Appendix 2). In addition to text message and email reminders, participants may also receive a follow-up phone call to prompt the completion of questionnaires at follow-up time points.

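### Error is held at 2.5% within each of three visits but nowhere across them, no visit is named primary, and the rule does not match the alpha used for the sample size

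*Protocol article*

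**What the plan says.** Under Statistical Analysis, significance of the primary efficacy analysis rests on Hochberg testing with the "family-wise error rate for each time point held at 2.5" percent. On the model, the same section says "The model will be fitted with ARFS at all follow-up points as the outcome variable", and then "The main analysis will use a generalized linear mixed model with the outcome at all time points and intention-to-treat principle". The Outcome Measures section gives the schedule: "Outcome measures will be completed via the Aim4Me website at baseline and at 3, 6, and 12 months". That makes three post-baseline visits.

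No primary time point, testing order or adjustment across visits appears in the Abstract, Aim, Primary Outcome Measures, Sample Size or Statistical Analysis sections. Neither the sidedness of the 2.5% nor the number of group comparisons in each family is given.

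The Sample Size section plans at alpha .05 and 80% power for a 2.2-point ARFS difference (SD 9.6), giving 300 per arm and 900 over three arms. It doubles this to 1800 for the analyses by sex ("Given that we also wish to examine this effect a priori in male and female subgroups separately") and then raises it to 2570: "To allow for 10% loss to follow-up at 3 months, 20% at 6 months, and 30% at 12 months".

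Before the model, the plan also has a set of t tests: "The outcome effects will first be evaluated using independent" t tests.

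**The concern.** Hochberg at 2.5% protects against a false claim among the group comparisons at one visit. Repeating it at three visits, with no visit ranked above the others, leaves the chance of a false claim at some visit uncontrolled. This is a rule that the article states, so it is not a detail left to an analysis plan.

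Three things are at stake.
- An effect seen only at 3 months would meet the same significance criterion as one still present at 12 months, in a trial described as lasting 12 months.
- The testing rule and the sample size use different alphas, so the stated 80% power does not describe the tests that will be run.
- The form of the economic evaluation depends on whether the change in ARFS or AQoL-6D is statistically significant, again with no visit attached.

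**Working it through.** **Inputs.** From Sample Size: difference 2.2, SD 9.6, alpha .05, power 80%, 300 per arm, 1800 evaluable, 30% loss at 12 months, total 2570. From Statistical Analysis: 2.5% per time point, Hochberg. From Outcome Measures: three follow-up visits. From Randomization: 1:1:1. The correlation between visits is not given; 0 to 0.9 is assumed. Tests are taken as two-sided unless noted.

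**1. Reproduce the plan's sample size.** n per arm = 2(z₀.₉₇₅ + z₀.₈₀)² × SD² / Δ² = 2(1.960 + 0.842)² × 9.6² / 2.2² = 298.9, so 299 (stated 300). One-sided .05 would give 236 and two-sided .025 would give 362. The stated figure is therefore one pairwise comparison, at one visit, at two-sided 5%.

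Inflation: 1800/0.9 = 2000, 1800/0.8 = 2250, 1800/0.7 = 2571. Only the 30% loss yields about 2570, so the 12-month visit sets the total.

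**2. Error across visits.** Bound: 3 × 0.025 = 7.5%. If the visits were independent: 1 − 0.975³ = 7.31%.

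Simulation under no effect anywhere (500,000 runs, three arms, three equally correlated visits, Hochberg at two-sided 2.5% within each visit) gives this chance of at least one false claim:

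| Between-visit correlation | Two comparisons with control | All three pairs |
|---|---|---|
| 0 | 7.0% | 6.7% |
| 0.5 | 6.3% | 6.1% |
| 0.7 | 5.6% | 5.4% |
| 0.8 | 5.2% | 5.0% |
| 0.9 | 4.4% | 4.2% |

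If the 2.5% is one-sided, each visit carries two-sided 5%. The two-sided bound is then 15%, 14.3% under independence, and 12.2% simulated at correlation 0.5 with two comparisons.

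**3. Power under the stated rule.** Power = Φ(Δ / (SD√(2/n)) − z₁₋α/₂). The first term is 2.2 / (9.6 × √(2/300)) = 2.807 for 300 per arm (one sex) and 3.969 for 600 per arm (pooled). With two comparisons, Hochberg rejects both if the larger p-value is at most α, and otherwise rejects the smaller if it is at most α/2.

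| Two-sided level | 300 per arm (one sex) | 600 per arm (pooled) |
|---|---|---|
| 5% | 80.1% | 97.8% |
| 2.5% | 71.4% | 95.8% |
| 1.25% | 62.1% | 92.9% |

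**4. After each remedy.**
- 12 months alone, Hochberg at two-sided 5%: error at most 5% (simulated about 4.8% with two comparisons, 4.5% with three). With two comparisons the steps are 5% and 2.5%, so sex-specific power lies between 71.4% and 80.1%.
- All three visits primary at 0.05/3 = 1.67% each: bound 5.0%, and 1 − (1 − 0.0167)³ = 4.92% if independent. The steps are 1.67% and 0.83%. Power is 66.0% and 56.7% within one sex, and 94.2% and 90.8% pooled.

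**The case against.** **The plan promises no overall 5%.** A reader might infer that a planned overall rate of 5% is breached. The documents do not support that. The .05 in Sample Size is the input for one comparison, and Statistical Analysis sets 2.5% per visit without naming a total. What stands is that the two figures differ and that no overall rate is held.

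**The excess is small.** Repeated scores on the same people are correlated, so 7.5% is a worst case. At a correlation near 0.8 the rate is about 5%, and at 0.9 it is below. This is right and limits the size of the point. It does not remove it, because the correlation is not given and the rule guarantees nothing below 7.5%.

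**No success rule is stated.** That the trial has three chances to succeed is something a reader might infer; the text does not say it. The model has a time-by-group term, so a fading effect would be visible in the estimates. Even so, nothing in the text prevents a primary claim from one visit alone.

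**The t tests and the analyses by sex.** A much larger error rate could be built by counting these as further primary claims. The documents do not support that either. Significance is tied to Hochberg and the mixed model, the t tests have no stated level, and the analyses by sex are to be examined a priori without being called primary.

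**Power in the pooled sample is ample.** It is 93 to 96% under the stated rule, so the shortfall concerns only the analyses by sex. Those analyses are why the sample was doubled, so the shortfall still touches a stated design aim. The model also adjusts for baseline ARFS, which would raise power by an amount that cannot be fixed from the documents; the figures here use the plan's own unadjusted basis.

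**Conclusion.** The point holds and should be fixed. Error is controlled within each visit and not across the three, with no primary time point. The bound is 7.5%. With two-sided tests the rate is about 5 to 6% for assumed correlations of 0.8 to 0.5, and 4.2 to 4.4% at 0.9.

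Separately, the testing rule does not match the sample size. At two-sided 2.5% the sex-specific power is 71% (62% at the smaller step with two comparisons), against the stated 80%. Pooled power remains 93 to 96%.

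Both parts depend on sidedness, which is not stated. If 2.5% is one-sided, it equals the two-sided 5% used for the sample size, and 80% holds at the larger Hochberg step (71% at the smaller). The two-sided error bound across visits is then 15%. Neither reading resolves both parts.

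**What to change.** Name 12 months, the visit that sets the sample size, as the single primary time point. Apply Hochberg at an overall two-sided 5% across the group comparisons there, and treat 3 and 6 months as secondary. If the sponsor prefers to keep all three visits primary, use 1.67% per visit and restate the power.

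In either case, state the sidedness, reconcile the alpha in Sample Size with that in Statistical Analysis, and say that the preliminary t tests are descriptive. Whether the analyses by sex are primary or secondary is the sponsor's choice.

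The cost is wording in the analysis plan and the registry entry while data collection continues. The change should be made before outcomes are examined by arm, since a time point chosen afterwards would not be credible. There are two downsides to the single-visit option: an effect seen only early can no longer be called the primary result, and the error allowed at 12 months rises from 2.5% to 5%. The three-visit option keeps early effects eligible but lowers sex-specific power to 57 to 66% per contrast with two comparisons.

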### Interventions

The intervention components are based on SDT, which focuses on the extent to which behaviors are self-initiated (autonomous) versus influenced by external factors (external motivators) [19]. SDT supports self-directed motivation by satisfying an individual’s need for autonomy, perceived competence, and relatedness. Autonomy will be satisfied by providing opportunities for participants to choose their own goals, reflect on progress and revise goals, access a range of resources that they self-select, and choose their level of engagement with the website. For Group 3, engagement with the dietitian will reinforce the importance of nutrition relative to personal motivators. The graphic design of the Aim4Me website and resource materials related to the motivators for, and barriers to, healthy eating among young adults. Website images, wording, and content have been selected based on feedback from this age group. In groups 2 and 3, perceived competence will be addressed by the self-development of personalized goals and regular self-monitoring of progress toward these goals to support progressive and small behavior change toward healthy eating.

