#### Engagement

Engagement will be measured using usage statistics captured by the website. The outcomes will include completion of the HEQ (control group only), the number of log-ins to the website, clicks on resources and links, views of personalized dietary feedback, and views and completion of goal setting and tracking (intervention groups 1 and 2). In addition, for intervention Group 2, engagement will be measured by attendance at the brief video consultation.

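### Mean (SD) is fixed as the summary for all counts with no provision for skewness; if website clicks and views are skewed, it hides how many participants never used a component and what typical use was

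*Protocol article*

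**What the plan says.** The Statistical Analysis section ends with a general presentation rule: "Data will be presented as mean (SD) for continuous and count variables". Counts are named explicitly and receive the same summary as continuous variables.

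The clearest count variables in the article are the engagement measures. The Engagement section states "Engagement will be measured using usage statistics captured by the website" and lists "the number of log-ins to the website, clicks on resources and links, views of personalized dietary feedback", together with views and completion of goal setting and tracking. It also lists measures that are not counts, such as completion of the Healthy Eating Quiz in the control group. For the arm offered the dietitian, "engagement will be measured by attendance at the brief video consultation".

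Engagement belongs to a declared aim: "The secondary aim is to investigate intervention reach, participant engagement, retention, satisfaction, and cost-effectiveness". On how evenly the website will be used, the article says only that participants can "choose their level of engagement with the website" (Interventions section). It gives no expected mean, spread or share of non-users for any engagement measure.

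**The concern.** Mean (SD) describes a count well when its distribution is roughly symmetric. Clicks and views on a website whose use is left to the participant may not be: some participants may never open a component and a few may use it heavily. The mean then sits above what most participants did, and neither the mean nor the SD says how many did nothing.

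Those two facts, the share of non-users and the typical level of use, are what a reader wants from an engagement result. They matter most if the primary comparison shows no difference and the question becomes whether the website was used at all. The article makes an explicit choice of summary here, so this is a comment on what is written and not on something left out.

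**Working it through.** **Plan's own figure.** The article states no figure for engagement, so there is nothing to reproduce. The sample size rests on the diet quality score and does not involve these counts.

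**Inputs.** From the article: the summary is mean (SD), and the counts are log-ins, clicks and views. Assumed, because the article is silent: a mean of 5 events per participant and a range of shapes, from Poisson to negative binomial with dispersion k, with or without 30% extra zeros.

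**Formulas.** Let m be the overall mean, π the share of extra zeros and μ = m/(1 − π).
- Without extra zeros: SD = √(μ + μ²/k) and P(0) = (k/(k + μ))^k. For Poisson, drop the μ²/k term and use P(0) = e^(−μ).
- With extra zeros: SD = √[(1 − π)(μ + μ²/k + μ²) − m²] and P(0) = π + (1 − π)(k/(k + μ))^k, with the same replacements for Poisson.

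**Numbers at m = 5.**
- Poisson: SD = √5 = 2.2; P(0) = e^(−5) = 1%.
- k = 2: SD = √(5 + 12.5) = 4.2; P(0) = (2/7)² = 8%.
- Poisson with 30% extra zeros: μ = 5/0.7 = 7.14; SD = √[0.7 × (7.14 + 51.02) − 25] = 4.0; P(0) = 30%.
- k = 0.5: SD = √(5 + 50) = 7.4; P(0) = (0.5/5.5)^0.5 = 30%.
- k = 0.25 with 30% extra zeros: SD = √[0.7 × (7.14 + 204.08 + 51.02) − 25] = 12.6; P(0) = 0.30 + 0.70 × 0.429 = 60%.

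Medians, quartiles and the share of use come from simulation (400,000 draws per shape). The simulated SD in the last row is 12.5, in line with the formula.

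| Assumed shape, mean 5 | Mean (SD) | Median (IQR) | Zero use | Share of all use by top 10% |
|---|---|---|---|---|
| Poisson | 5.0 (2.2) | 5 (3–6) | 1% | 18% |
| Negative binomial, k = 2 | 5.0 (4.2) | 4 (2–7) | 8% | 28% |
| Poisson, 30% extra zeros | 5.0 (4.0) | 6 (0–8) | 30% | 23% |
| Negative binomial, k = 0.5 | 5.0 (7.4) | 2 (0–7) | 30% | 45% |
| Negative binomial, k = 0.25, 30% extra zeros | 5.0 (12.5) | 0 (0–4) | 60% | 70% |

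**Reading the table.**
- In the first two rows mean and median nearly agree, and mean (SD) is adequate.
- In the last two rows the same mean goes with a median of 2 or 0.
- The second and third rows have almost the same mean (SD), yet 8% and 30% non-users. Mean (SD) cannot tell these apart.

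**Other assumed means.** The pattern is the same. With k = 0.5, a mean of 3 gives median 1 and 38% zeros, and a mean of 10 gives median 4 and 22% zeros. With k = 0.25 and 30% extra zeros, means of 3 and 10 both give median 0, with 64% and 55% zeros.

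**The case against.** Four things can be said for the plan as written.

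1. *The skew is assumed.* This stands. A reader might infer that the engagement counts will have many zeros and a few heavy users. The article does not say so; it says only that use is self-directed. For log-ins it points the other way. Participants log in to start the baseline questionnaires (Screening and Baseline Assessments), randomization follows baseline data collection (Study Design), and follow-up outcomes are also completed on the website (Outcome Measures). If all log-ins are counted, every randomized participant has at least one. Voluntary clicks and views have no such floor.

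2. *Counts are not the whole engagement result.* This also stands. A reader might infer that, with no engagement model stated, mean (SD) is all that will be reported and the secondary aim will be answered with a misleading figure. But completion and attendance are naturally reported as proportions and show non-use directly. An analysis plan that is not shown may add summaries or models, and its absence here is no fault of the article.

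3. *An SD above the mean already warns of skew.* This stands in part. It would do so in the last two rows of the table. It would not in the third, where 30% are non-users and the SD is below the mean. Even where it warns, it gives neither the share of non-users nor typical use.

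4. *A handful of users will not make arms look different.* A reader might fear this. With about 857 participants per arm (2570/3) and the most extreme SD above, the standard error of a difference in means is √(2 × 12.5²/857) = 0.60 against a mean of 5. Chance differences driven by a few users would therefore be modest, and a mean count remains a valid measure of average use.

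**Conclusion.** The point holds in a limited, conditional form. The article fixes mean (SD) for every count without provision for skewness. If the click and view counts prove skewed, that summary alone would hide the share of non-users and the typical level of use, which would weaken the answer to the engagement part of the secondary aim.

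The size depends wholly on the unknown shape. The loss is negligible under Poisson or mild overdispersion. It is material under strong overdispersion or excess zeros, where a mean of 5 could stand for a median of 0 to 2 with 30% to 60% non-users. These shapes are illustrations and not values from the article.

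This is a minor reporting improvement. The primary analysis, its error rate and the sample size are unaffected.

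**What to change.** Replace the closing sentence of the Statistical Analysis section with wording such as:

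> Continuous variables: mean (SD), or median (IQR) if skewed. Count variables: mean (SD) together with median (IQR) and the percentage with zero use, by group.

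The percentage with zero use is the most informative addition, because a median of 0 says little about the amount of use among those who did engage. Keeping the mean preserves average use. Settling this before the engagement data are summarised also avoids choosing the summary after seeing them.

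The cost is one sentence and a wider table. No new data are needed and nothing is lost. No regression model for engagement is called for on this ground.
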